### **6.1.2. Sputum conversion**

- Participant with sputum smear converted following the standard two-month intensive phase treatment.

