#### **4. HYPOTHESIS**

- The use of a digital medication event reminder and monitor device-observed self-administered therapy provides a non-inferior medication adherence and treatment outcomes for patients with TB compared with the standard in-person DOT in Ethiopia, one of the low-income countries with the highest burden of TB

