#### **5.1.2. Treatment outcomes**

To assess whether MERM-observed self-administered therapy improves treatment outcomes in patients with TB compared with the standard DOT.

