#### **8.5.1.2. Inclusion criteria**

Inclusion criteria will include:

- Patients with new, or previously treated, bacteriologically-confirmed drug-sensitive pulmonary TB
- Eligible to start the standard 6-month first-line anti-TB medication
- Outpatient status at the time of screening and enrollment
- Men or women age  $\geq 18$  years
- Able and willing to provide informed consent

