#### **8.5.1.5. Sampling and sample size**

The sample size is calculated considering a 1-sided type I error of 2.5%, a power of 80%, 10% attrition rate, delta of 20%, non-inferiority margin, and a continuous outcome of percentage adherence over the two-month intensive phase, with a standard deviation of 36% and 79% of average adherence, assuming null hypothesis for both arms. The results yield a sample size of 57 in each arm for a total of 114 participants. We will do a  $\log_{10}$  transformation on the data, where a difference can be equivalently transformed into a ratio using a power ( $10^3$ ). The non-inferiority will be calculated as the log in the control minus the log in the intervention, which is equivalent to the log of the control divided by intervention.

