## **8.7. Study procedure**

The main data collection tools will include

- a baseline patient information questionnaire (demographic, socioeconomic, behavioral, social, and clinical information),
- medication adherence measurement tools (MERM vs. DOT daily treatment adherence monitoring tool and urine colorimetric isoniazid test - IsoScreen™ test, GFC Diagnostics Ltd, Bicester, England, and adherence self-report questionnaire),
- clinical measurement tools (pre-post treatment sputum Xpert MTB/RIF assay or microscopy and adverse treatment outcome monitoring tool),
- cost/economic tools (health-related quality of life [HRQoL], catastrophic cost, post-diagnostic cost from an individual patient's perspective, predictors of HRQoL and catastrophic costs,

- Usability and treatment satisfaction tools (treatment satisfaction questionnaire for medication version 1.4 (TSQM v1.4) tool and an 18-item treatment satisfaction questionnaire)

The study investigators will identify healthcare providers in the TB clinics and provide training on the study procedures, how to operate the evriMED500 device, and perform a urine isoniazid test. The investigators will perform a 1:1 randomization of participants before the start of the study using computer-generated random numbers. Providers will enroll participants in the two arms sequentially as they arrive in the clinic and the investigators will routinely monitor the process. Providers will provide instruction using the Amharic version of the study's participant information sheet. Providers will recruit participants and obtain written informed consent in the local language, which is Amharic. The consent form will also function as an acknowledgment of personal responsibility keeping the device properly and returning upon completion of the study.

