#### **8.8.8. Bacteriologically confirmed TB case**

- A patient from who has at least one positive result either by smear microscopy, culture or Xpert MTB/RIF assay.

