### **11.2. Unexpected or adverse events**

Given that the study is neither dictating the need for treatment of TB or specific regimen, serious adverse events will not be directly attributable to the study. The study will not dictate diagnosis or treatment algorithms for TB, and all diagnoses testing assays and treatment regimens will follow the Ethiopian national guidelines; thus, it will not introduce or prescribe new drugs. The major risks of this screening program are related only to pill-taking mechanisms. Both adverse events and serious adverse events will be reported to the EFDA in line with the stipulated timeline irrespective of relatedness to

the study procedure. Adverse reactions to TB medications will not be considered the outcomes of the study. The investigators will capture these events only to the extent they are available in the study health facilities' records and registries. The investigators will conduct chart abstractions to review adverse events that are related to TB treatment, as recorded from the TB clinic registries. For patients who are co-infected with HIV, the chart review will also include the type of HIV regimens, viral load, CD4 counts, and other co-infections diagnosed and treated.

Regarding TB diagnosis, at the initial stage or following the intensive phase, there could be discrepancies between the health facility results (Smear microscopy or Xpert MTB/RIF) and the study result (MGIT liquid culture). In this case, the investigators will communicate the results to the healthcare providers for their review and decision.

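### Smear conversion is a primary outcome under a non-inferiority hypothesis, but the protocol gives it no margin, no power and no requirement of a positive smear at entry

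*Protocol*

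**What the plan says.** **Claim and outcome.** Section 4 says that the intervention "provides a non-inferior medication adherence and treatment outcomes for patients with TB compared with the standard in-person DOT in Ethiopia". The Synopsis and 6.1.2 list two primary outcomes: percentage adherence, and "Participant with sputum smear converted following the standard two-month intensive phase treatment". The matching objective in 5.1.2 is worded as superiority: "To assess whether MERM-observed self-administered therapy improves treatment outcomes in patients with TB compared with the standard DOT".

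**Sample size.** Section 8.5.1.5 uses one-sided 2.5% error, 80% power, 10% attrition, a 20% margin, an SD of 36% and mean adherence of 79%, for "a continuous outcome of percentage adherence over the two-month intensive phase". It arrives at 57 per arm. It judges non-inferiority by a difference of log-transformed values.

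**Analysis.** Section 9 does not mention sputum conversion. It provides chi-square tests of association for categorical variables in general and a 5% significance threshold throughout.

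**Who enters.** Section 8.5.1.2 admits "Patients with new, or previously treated, bacteriologically-confirmed drug-sensitive pulmonary TB". Section 8.8.8 defines confirmation as "at least one positive result either by smear microscopy, culture or Xpert MTB/RIF assay".

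**Which test.** Section 6.1.2 refers to smear, and the laboratory text in 8.7 assigns AFB microscopy to the check for conversion. The tool list in the same section has "pre-post treatment sputum Xpert MTB/RIF assay or microscopy". Section 11.2 foresees "discrepancies between the health facility results (Smear microscopy or Xpert MTB/RIF) and the study result (MGIT liquid culture", both at the start and after the intensive phase. No procedure in 8.7 describes such a culture.

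**The concern.** Half of the headline hypothesis concerns treatment outcomes, and conversion is the primary outcome that would carry it. To declare non-inferiority one needs a margin fixed in advance and a confidence limit to set against it. The protocol supplies a margin for adherence and nothing for conversion. A non-significant chi-square test is not evidence of non-inferiority, and in a trial of this size it is an easy result to obtain.

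The outcome also does not fit the population. A participant confirmed by Xpert or culture with a negative smear at entry has nothing to convert. The protocol neither leaves such participants out of the conversion analysis nor says how they count. If they stay in, the difference between arms is pulled towards zero, which in a non-inferiority comparison is the favourable direction.

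Finally, two passages on the sputum test do not agree with the outcome definition. A site could therefore read the protocol as allowing a different test before and after treatment.

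**Working it through.** **1. The plan's own figure.** Inputs from 8.5.1.5: margin 20, SD 36, true difference 0, z = 1.960 and 0.842.

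n per arm = 2 × [(1.960 + 0.842) × 36 / 20]² = 50.9, so 51. With 10% attrition, 51 / 0.9 = 56.7, so 57 per arm and 114 in total. The figure reproduces, for adherence. Neither the SD nor the log-difference rule carries over to a yes/no outcome.

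**2. Power that the same participants give for conversion.** The protocol states no conversion rate and no conversion margin, so both are assumed over a range. The rate p is taken as equal in both arms, with one-sided 2.5% error:

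power = Φ( margin / √(2p(1−p)/n) − 1.96 )

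Two values of n are used: 51 (all evaluable participants) and 38 (if an assumed 75% are smear-positive at entry, 51 × 0.75 = 38.25).

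| Assumed conversion | n = 51, 10 points | n = 51, 20 points | n = 38, 10 points | n = 38, 20 points |
|---|---|---|---|---|
| 80% | 24% | 71% | 19% | 59% |
| 85% | 29% | 81% | 23% | 68% |
| 90% | 39% | 92% | 31% | 83% |
| 95% | 64% | >99% | 52% | 98% |

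Example: p = 0.85 and n = 51 give a standard error of √(2 × 0.85 × 0.15 / 51) = 0.0707. For 10 points, Φ(1.414 − 1.96) = 0.29. For 20 points, Φ(2.829 − 1.96) = 0.81.

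The 95% CI half-width with 51 per arm is 1.96 × standard error: 15.5 points at 80% conversion, falling to 8.5 points at 95%. The smallest margin with 80% power is 2.80 × standard error: 22, 20, 17 and 12 points at 80, 85, 90 and 95%.

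**3. Effect of smear-negative entrants.** Let f be their share, equal in the two arms, and d the true deficit among smear-positive participants. Suppose every smear-negative entrant is counted as converted. The conversion rate in each arm is then f + (1−f)p, and the observed deficit is (1−f)d. For d = 15 points:

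- f = 20%: 0.8 × 15 = 12 points
- f = 40%: 0.6 × 15 = 9 points

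If they are all counted as not converted, the rate is (1−f)p. The risk difference shrinks by the same factor, and failures unrelated to treatment are added. If they are left out, there is no dilution. The documents give no value for f; 20% and 40% are assumptions.

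**4. The sputum test, place by place.**

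| Place | Test |
|---|---|
| 6.1.2 | smear |
| 8.7, laboratory text | AFB microscopy for conversion |
| 8.7, tool list | Xpert or microscopy, before and after |
| 11.2 | MGIT culture as the study's own result |

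The first two agree. The third allows an alternative, and the fourth refers to a test that the procedures do not contain.

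**The case against.** **The sputum test is fixed.** The outcome line names smear only, and 8.7 assigns AFB microscopy to conversion. Elsewhere in 8.7, Xpert is tied to the sites' own treatment decisions, and 11.2 concerns diagnostic discrepancies. This stands. A reader might infer that the outcome itself rests on three assays, and the text does not support that. What remains is that the tool list and 11.2 need to be brought into line.

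**The dilution is conditional.** Conversion ordinarily means positive to negative, and the protocol nowhere says that a smear-negative entrant counts as converted. This also stands. A reader might infer that a bias is already built in. It arises only if these participants stay in the analysis set, and its size depends on an unknown share.

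**The trial may be large enough.** With a 20-point margin and 51 evaluable per arm, power is about 80% or more once conversion reaches 85%. So the inference that 114 participants cannot support the claim goes too far. But the 20% in 8.5.1.5 is set for adherence, and nothing extends it to conversion.

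**A missing margin does not make every result non-inferior.** That is correct. Its consequence is that non-inferiority on conversion cannot be declared from the protocol as written.

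**The statistical analysis plan may settle this.** It may well hold the coding rules and the model. But the protocol itself sets margin and power, and does so for one of two primary outcomes while claiming non-inferiority for both. A separate plan also leaves the conflicting assay wording in the protocol in place.

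**Conclusion.** The concern holds in this form. The protocol claims non-inferior treatment outcomes and makes smear conversion primary, but it sizes and sets a margin for adherence only. The one stated test that could apply examines association. Eligibility lets in participants who cannot have the outcome, and two passages on the sputum test are unreconciled with the other two.

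The size of the power problem is open. Over assumed conversion of 80 to 95%, power runs from 24 to 64% at 10 points and from 71 to over 99% at 20 points with 51 per arm, and from 19 to 52% and 59 to 98% with 38 per arm. The firm defect is the absence of a decision rule and of a defined evaluable population. Low power is a consequence only under some of these assumptions.

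**What to change.** 1. In 6.1.2, define the outcome as AFB-smear negative at month two among participants who were AFB-smear positive at baseline, with the same test at both times. State how death, loss to follow-up and missing sputum are counted.
2. Reconcile the tool list in 8.7 and the culture wording in 11.2 with 6.1.2 and the laboratory text of 8.7.
3. In Section 9, name the analysis of conversion: risk difference between arms with 95% CI.
4. Then choose one of two courses. Either limit the non-inferiority claim in the Synopsis and Section 4 to adherence, and report conversion as an estimate with its interval. Or state and justify a conversion margin, and give the power that 114 participants provide at a stated conversion rate, allowing for the smear-negative share. Word objective 5.1.2 to match.

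The cost is a change of wording, a smaller set for the conversion analysis and, on the first course, a narrower headline claim. Stating a margin leaves the claim intact, but may show that the planned number is too small for it.

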## **6.2. Secondary outcomes**

### **6.2.1. Negative IsoScreen urine isoniazid test**

- Number of participants with negative IsoScreen urine isoniazid test.

### **6.2.2. Adverse treatment outcome**

- Participants having at least one of the three events: treatment not completed; death; or loss to follow-up.

### **6.2.3. Self-reported adherence**

- Participants who self-reported to have forgotten to take their medication.

### **6.2.4. Health-related quality of life (HRQoL)**

- The association between MERM-observed therapy and HRQoL, with the HRQoL measured and calculated for each

### **6.2.5. Catastrophic costs**

- Participants with overall TB treatment cost exceeding or equivalent to 20% of their income.

### **6.2.6. Post-diagnostic cost from an individual patient's perspective**

- Participant's cumulative direct costs (out-of-pocket costs related to anti-TB drug pick-up) and indirect costs (guardian and coping costs) over the two-month intensive phase.

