Ethiopia, where the proposed study will be conducted, is among countries highly encumbered by the TB epidemic, and one of the least resourced in the world. According to the 2018 global TB report, there were 117,705 TB cases reported in the country, and of the annual \$93 million needed for TB care and control, the country's domestic contribution was only 11%. Despite TB care and treatment services being delivered free of charge, TB patients are facing out-of-pocket payments and income losses due to transportation, accommodation, and food to get treatment at healthcare facilities: tackling their adherence to treatment and forcing them to stop working, sell their properties, borrow money and reduce their overall income. These, in turn, are increasing rates of loss to follow-up, disease relapse, and drug resistance. The spread of TB due to patients traveling daily to healthcare facilities for medication is increasing the transmission potential of the disease, especially in the capital city Addis Ababa, where mobility is making the city crowded - as manifested through housing conditions and the public transport. Different studies conducted in Addis Ababa reported that TB patients consider their daily DOT visits as pointless, and providers see DOT as a very challenging strategy for TB patients. As a result, daily DOT survives in principle, while implementation is irregular as both TB patients and providers have uncertainties with it. Providers witness that TB patients prefer taking the tablets at home once they have the necessary advice and counseling. Patients complain that they travel for daily DOT on foot under exhaustive road conditions for up to two hours and 2.5 kilometer, taking several rests on their way because of their sickness. They spend much on transportation and some of them get fired from their job as they were absent for the daily DOT. Providers witness how patients are seen when they exhaust, and patients took their daily DOT with dissatisfaction. Some patients claim that once they are informed of the disease on day one, no one talks to them the following days and they just swallow the drug and go back. Besides, they face stigma on their way to daily DOT, and they change their name in the TB clinic for they do not want to be notified as TB patients. The challenge is similar in other parts of Ethiopia. According to the WHO 2018 report, TB treatment coverage in the country is 68%, which is minimum even to accommodate the current DOT need. The estimated percentage of MDR/RR TB cases is significantly higher in previously treated cases [14% (6.7–25)] than new cases [2.7% (1.6–4.1)]; which indicates that management of TB treatment under DOT is problematic in the country. There were 680 MDR/RR-TB and four XDR-TB laboratory-confirmed cases in the country in 2017, while many more were left undiagnosed due to limited availability of the service.

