### **5.2. Secondary objectives**

#### **5.2.1. HRQoL and catastrophic cost**

To evaluate if MERM-observed therapy provides higher HRQoL and lower catastrophic costs compared to the standard DOT

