## **9. STATISTICAL ANALYSIS**

Descriptive summary measures will be used to report participant characteristics. Chi-square tests will be used to evaluate potential associations among categorical variables. To compare the level of adherence between study arms and among variables, independent t-tests will be done on log-

transformed adherence percentage of the expected 60 days. Effects of the arms and other adherence variables will be estimated using a geometric mean (GM) with geometric standard deviation (GSD) and mean ratios (MR) with 95% confidence intervals (CI). Log binomial regression will be conducted to identify risk factors of at least one negative isoniazid urine test and self-reported adherence of participants. Effects will be measured using adjusted relative risk (ARR) with 95%CI. A general linear model will be done on log-transformed adherence percentage to identify the effects of variables on participants' level of adherence. Effects will be measured using an adjusted mean ratio (AMR) with 95% CI.

Descriptive statistics including frequency and percentage will be used to describe the health state of the study participants. Multiple bar charts with cross-tabulation will be used to illustrate distributions of health states by study arms. Chi-square and Fisher's exact tests will be employed to compare the five EQ-5D-5L health domains by study arms. Kolmogorov–Smirnov, Shapiro–Wilk tests, and median values with interquartile range (IQR) will be used to summarize EQ-5D-5L index value/utility. Nonparametric Mann–Whitney U test will be employed to compare the difference in EQ-5D-5L index value/utility among study arms. A log-binomial model will be used to identify risk factors for lower HRQoL, which is having at least one health problem.

The overall TB treatment cost will be estimated by considering costs related to anti-TB drug pick-up, guardian costs, and coping costs over the two-month intensive phase. The proportion of study participants who faced catastrophic costs at a cut-off point of 20% will be estimated. A cross-tabulation will be employed to evaluate the distribution of catastrophic cost over the study arms and chi-square test will be used to test the association between catastrophic cost and study arms.

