#### **12.5. Payment for participation**

There will be no payment for participation, either in cash or in-kind, to patients in the intervention or DOT arm, or healthcare providers, as this would influence outcomes of the study. However, if the participants are coming just for the purpose of the study, they will be reimbursed for transport.

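### The cost and catastrophic-cost outcomes do not count the patient's own lost income or time, although the rationale names income and job loss as burdens of daily DOT

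*Protocol*

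**What the plan says.** Section 6.2.6, like item 8 of the synopsis outcome list, defines the post-diagnostic cost as direct costs, meaning out-of-pocket spending to collect the drugs, plus "indirect costs (guardian and coping costs) over the two-month intensive phase". Section 9 gives the same components for the overall treatment cost behind the catastrophic-cost outcome: "costs related to anti-TB drug pick-up, guardian costs, and coping costs over the two-month intensive phase". Section 6.2.5 classifies as catastrophic "Participants with overall TB treatment cost exceeding or equivalent to 20% of their income", and Section 9 adds "The proportion of study participants who faced catastrophic costs at a cut-off point of 20% will be estimated". No section gives the period of that income or says whether it is individual or household income.

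The rationale in 2.1 says that "TB patients are facing out-of-pocket payments and income losses due to transportation, accommodation, and food to get treatment at healthcare facilities". It adds of patients that "some of them get fired from their job as they were absent for the daily DOT". The objective that these outcomes serve (5.2.1) is "To evaluate if MERM-observed therapy provides higher HRQoL and lower catastrophic costs compared to the standard DOT".

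Section 8.6 has control participants attend on every business day of the two-month intensive phase and intervention participants every 15 days. Section 8.7 names a patient-cost tool, administered to participants at the end of the intensive phase, without describing its items.

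**The concern.** The component list names the guardian's costs but not the patient's own lost earnings or time. That loss is one of the burdens the rationale uses to argue against daily DOT, and it recurs with every visit. The arms differ by design in the number of visits. A cost that accrues per visit and is not counted is therefore missing mainly from the DOT arm, and the comparison for the objective in 5.2.1 may show a smaller MERM advantage than patients experience.

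This is not a detail left open for a statistical analysis plan. The protocol states a list of components twice, in the outcome definition and in the analysis section, and a later plan could add lost income only by departing from it.

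Two lesser matters belong to the same definition. Coping costs are not defined. The cost is fixed to two months, while the income it is compared with has no stated period.

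**Working it through.** **The plan's own figures.** The protocol gives no expected value, variance or sample size for the cost outcomes, so there is no cost figure to reproduce. The only computed design figure is the sample size in 8.5.1.5. With margin 20, SD 36, one-sided 2.5% and 80% power, n = 2 × (1.96 + 0.84)² × 36² / 20² gives 51 per arm after rounding up, and 51 / 0.9 = 56.7, so 57. This matches the stated 57 per arm. It rests on adherence and is unaffected by this point.

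**What is counted and what is named as a burden**

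| Item | Rationale (2.1) | Outcome (6.2.6) | Analysis (Section 9) |
|---|---|---|---|
| Out-of-pocket cost of attending | yes | yes | yes |
| Patient's own income or job loss | yes | not listed | not listed |
| Guardian costs | not by name | yes | yes |
| Coping costs | borrowing and sale of property described, term not used | yes, undefined | yes, undefined |

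**Illustration of the size**

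Inputs from the protocol:
- 60 expected treatment days (Section 9).
- Control attendance on business days and intervention attendance every 15 days (8.6).
- Travel of up to two hours (2.1).

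Assumptions: five business days a week, full attendance as scheduled, an 8-hour working day, and every hour displacing paid work. The two hours are read as time per trip.

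- Control visits: 60 × 5/7 = 42.9.
- Intervention visits: 60 / 15 = 4.
- Excess visits: 42.9 − 4 = 38.9.
- Working time in two months: 42.9 × 8 = 342.9 hours.

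| Hours per trip | Omitted excess (hours) | Share of two-month working time |
|---|---|---|
| 0.5 | 38.9 × 0.5 = 19.4 | 19.4 / 342.9 = 5.7% |
| 1 | 38.9 × 1 = 38.9 | 38.9 / 342.9 = 11.3% |
| 2 (upper figure in 2.1) | 38.9 × 2 = 77.7 | 77.7 / 342.9 = 22.7% |

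Amounts in the lower part of this range can still change a participant's classification. With two-month income as the denominator, counted costs of 10% fall below the 20% cut-off; adding lost earnings of 10% brings the total to 20%, which meets it.

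**Effect of the unstated income period.** The cut-off is 0.20 × (months of income used). Dividing by 2 expresses it as a share of two-month income.

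| Income period (assumed) | Cut-off in months of income | As share of two-month income |
|---|---|---|
| 1 month | 0.2 | 10% |
| 2 months | 0.4 | 20% |
| 6 months | 1.2 | 60% |
| 12 months | 2.4 | 120% |

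The range is 12-fold. On annual income, two-month costs would have to exceed the whole of two-month income before they counted as catastrophic.

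**The case against.** The strongest reply is that the definition may be fuller than it looks. Coping costs are undefined, and the burdens listed in 2.1 include stopping work and reduced income alongside borrowing and selling property. The named cost tool may also record lost income. This stands as a reason to ask for a definition. It does not put lost income into the sum, because 6.2.6 and Section 9 decide what is added and neither names it.

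A reader might go further than the protocol allows in several ways:

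- **That lost time is the component on which the arms differ most, so the comparison is certainly biased towards no difference.** Transport to collect drugs is counted and follows the same 43 versus 4 visits, and nothing in the protocol ranks the two. Only a possible understatement can be claimed.
- **That the omitted item alone exceeds the 20% cut-off.** This holds only if the upper travel time applies to every visit. Section 2.1 calls DOT implementation irregular, 8.7 foresees self-administered doses in the control arm, and 8.6 expects some unemployed participants and moves some intervention participants to daily DOT. The excess of 38.9 visits is a ceiling.
- **That costing two of six months is an error.** The window is stated openly, and under 8.6 both arms follow the same standard DOT practice afterwards. It covers the only phase in which the arms differ.
- **That coping costs are double-counted.** This would follow only if the term means loans and asset sales that pay for items already in the sum, which the protocol does not say.
- **That the 20% cut-off has no meaning.** The income period could be settled in an analysis plan not shown here. It needs clarifying but is not an error in itself.
- **That reimbursement distorts the costs.** Section 12.5 says "if the participants are coming just for the purpose of the study, they will be reimbursed for transport". Those are study-only trips and not drug pick-up, so no change is needed there.

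**Conclusion.** The point holds in a limited form. The stated components omit the patient's own lost income or time, a visit-related cost that the rationale names and that falls mainly on the DOT arm. Followed as written, the two cost outcomes may understate a MERM advantage on the objective in 5.2.1.

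The plausible size is about 6% to 23% of two-month working time. That depends on the assumptions of full attendance, 8-hour days and every hour displacing paid work, and the top of the range uses the protocol's maximum travel time. The direction rests on the visit schedules alone; the amount cannot be known from the document.

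The undefined coping costs and the unstated income period are supporting clarifications. Only secondary outcomes are affected; the primary outcomes and the sample size stand. The change is still worth making, because the gap bears directly on an objective of the trial and costs little to close.

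**What to change.** 1. In 6.2.6, the matching synopsis item and Section 9, add the patient's own lost income or time for drug pick-up to the indirect costs, or state why it is excluded.
2. Define coping costs. If loans and asset sales finance items already counted, report them separately and leave them out of the sum.
3. In 6.2.5 and Section 9, set the two-month cost against income over the same two months, and state whether income is individual or household.

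The cost is wording plus at most a few items in the patient-cost interview already planned for participants. There is a small downside: self-reported income loss is noisy, and the total will differ from the one under the current definition. Reporting the total with and without the added component would keep both visible.
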